## Abstract

**Background:**

Foot problems in general and forefoot problems in particular can lead to a decrease in mobility and a higher risk of falling. Forefoot problems increase with age and are more common in women than in men. Around 20% of people over 65 suffer from non-traumatic foot problems and 60% of these problems are localised in the forefoot. Little is known about the best way to treat forefoot problems in older people. The aim of this study is to compare the effects of two common modes of treatment in the Netherlands: shoe advice and podiatric treatment. This paper describes the design of this study.

**Methods:**

The study is designed as a pragmatic randomised clinical trial (RCT) with 2 parallel intervention groups. People aged 50 years and over who have visited their general practitioner (GP) with non traumatic pain in the forefoot in the preceding year and those who will visit their GP during the recruitment period with a similar complaint will be recruited for this study. Participants must be able to walk unaided for 7 metres and be able to fill in questionnaires. Exclusion criteria are: rheumatoid arthritis, neuropathy of the foot or pain caused by skin problems (e.g. warts, eczema). Inclusion and exclusion criteria will be assessed by a screening questionnaire and baseline assessment. Those consenting to participation will be randomly assigned to either a group receiving a standardised shoe advice leaflet (n = 100) or a group receiving podiatric treatment (n = 100). Primary outcomes will be the severity of forefoot pain (0-10 on a numerical rating scale) and foot function (Foot Function 5-pts Index and Manchester Foot Pain and Disability Index). Treatment adherence, social participation and quality of life will be the secondary outcomes. All outcomes will be obtained through self-administered questionnaires at the start of the study and after 3, 6, 9 and 12 months. Data will be analysed according to the "intention-to-treat" principle using multilevel level analysis.

**Discussion:**

Strength of this study is the comparison between two common primary care treatments for forefoot problems, ensuring a high external validity of this trial.

**Trial registration:**

Netherlands Trial Register (NTR): NTR2212

## Background

Pain and discomfort due to foot problems are common and increase with age. Population-based surveys have estimated the prevalence of foot problems between 14.9 and 41.9% for people aged 50 years and older [1-4]. The prevalence of foot problems was found to be higher in women than in men [2,5]. Not all foot problems or foot deformities lead to pain or functional limitations [5-7] but people with disabling foot pain have been shown to experience a lower degree of well-being [2] and to have a higher risk of a decrease in mobility [2,8] and falling [9,10].

Forefoot problems including metatarsalgia, hallux valgus and hallux rigidus are the most common foot problems in older people [2,5,9]. A community-based study among 5689 older people in the Dutch area of Apeldoorn (a mixed urban-rural area) showed a prevalence rate of forefoot problems of 60% within the group of people reporting non-traumatic foot problems (n = 1130) [2]. In an English population survey among 3417 adults, more than one-third indicated to have pain in the great toe or in the first metatarsophalangeal joint (MTP-joint), and 9.5% indicated to be disabled by their foot problem [5].

Underreporting of foot problems is an acknowledged phenomenon in healthcare [9-11]. The community-based survey among older people in The Netherlands [9] showed that only 56% of the respondents sought health care, by consulting their general practitioner (GP) (46%), a medical specialist (36%) (mainly orthopaedic surgeons) or an allied health care professional (18%) (mainly podiatrists). A GP will commonly refer non-traumatic foot problems to a podiatrist or will treat the patient him or herself. Dutch podiatric care starts with an assessment which includes medical history, detailed analysis of the anatomical relationships within the foot and both a postural and a gait analysis [12]. Treatment may consist of (or a combination of) construction of full length podiatric insoles, silicone toe devices, (shoe) advice or basic foot and nail care. The treatment by the GP usually consists of prescribing pain medication (simple analgesic or non-steroidal inflammatory drugs [NSAIDs]) or by giving lifestyle advice (e.g. try to lose weight, improve shoe wear) [13].

The primary cause of non-traumatic forefoot problems can be very diverse and includes the possible influence of ill-fitting shoes [14,15]. Some evidence exists that ill-fitting footwear is associated with foot problems such as corns, calluses, hallux valgus and lesser toe deformities. Both the advice to buy well-fitting shoes and referral to a podiatrist are common treatment modalities of Dutch GPs. Whether these treatments actually lead to improvement of non-traumatic forefoot problems is not known, nor is it known if one treatment is more effective than the other.

The aim of this article is to describe the protocol of a pragmatic randomised clinical trial to compare the effectiveness of two common treatments for forefoot problems in older people and to discuss (or comment on) the choices made in the design. The primary objective of the trial is to investigate the effectiveness of podiatric treatment versus standardised shoe advice in people aged 50 years and older with disabling forefoot pain. The secondary objective is to conduct a process evaluation of the podiatric treatment provided for forefoot pain in this trial.

## Method

### Trial design

This study is designed as a pragmatic open randomised clinical trial with 12 months follow-up. Participants will be recruited via general practice clinics (figure 1); those who are eligible and give written consent to participation will be randomly assigned to either the intervention group or the control group. The Medical Ethics Committee of the VU University Medical Centre in Amsterdam has approved the design of this study (No. 2009/267).

**Figure 1 F1:**
[figure not shown]
Design of the RCT

### Participants

General practice clinics affiliated with the Academic Network for GPs of the VU University Medical Centre in Amsterdam will partake in this study. Recruitment of participants will be from patients who have visited their GP with non traumatic pain in the forefoot in the preceding year and those who will visit their GP during the recruitment period with a similar complaint. Participants, aged 50 or over, will have non-traumatic pain around the MTP-joints (figure 2) or further distally of at least one month's duration. The pain will be due to a musculoskeletal forefoot problem and the participants indicate to be functionally disabled because of this ailment. Participants will be excluded if they have received treatment for this problem in the previous six months or if the pain is caused by rheumatoid arthritis, a recent trauma, an operation, or by a non musculoskeletal problem (e.g. warts or a fungal infection of the foot). Additionally, patients with diabetic neuropathy of the feet or with foot problems that are deemed to be too serious by either the GP or by the study team to be treated in primary care will be excluded. Patients with rheumatoid arthritis or diabetic neuropathy are excluded from this trial because Dutch medical guidelines [16]indicate that these patients should be referred for podiatric care in all cases. Participants who are not able to walk 7 meters without a walking aid are also excluded, as they will not be able to perform the foot pressure measurements.

**Figure 2 F2:**
[figure not shown]
**Foot manikin screenings questionnaire **[5]. "I" is the inclusion area.

### Inclusion procedure

Potential participants will be recruited by three different methods. First, in all participating practices a retrospective search of the medical records will be carried out to identify all people aged 50 and over who have consulted their GP for a forefoot problem in the year preceding the start of the study. Second, all older people who consult their GP for forefoot problems during a period of 12 months following the start of the study will be considered for participation (prospective recruitment). Finally, all people visiting the general practice (for any reason) will be informed about the study by putting up posters in the waiting area of the GP clinics inviting patients to contact their GP if they have forefoot pain.

All potentially eligible patients will be invited to participate in the study and will receive comprehensive information about the study, a screening questionnaire and a pre-paid envelope to return the consent form and the questionnaire. Non-responders will receive a reminder after 2 weeks.

In addition to the assessment by the GP, inclusion and exclusion criteria will be assessed using self-report information from the screening questionnaire. Forefoot pain intensity is scored using a 0-10 point numerical rating scale and the location of pain is indicated on a foot manikin [17]. The area that will lead to inclusion in the study is shown in figure 2. Foot disability is assessed by the Foot Pain and Disability Index (FPDI) [17,18].

All patients who are potentially eligible for the study based on the screening questionnaire will be invited for a foot examination details of which will be discussed below (see Foot examination). The purpose of the foot examination is to measure baseline foot and pressure characteristics and to assess eligibility to participate in the trial. If the foot problem of the patient is considered to be too severe, and neither podiatric treatment nor shoe advice is considered adequate treatment, or if there are signs of any of the exclusion criteria like diabetic neuropathy, the patient will be referred back to their GP. If patients meet all eligibility criteria, written consent to participation in the trial will be obtained and a unique study number will be allocated to the participant.

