### Primary and secondary outcome measures

The primary outcome measures will be forefoot pain intensity scored by the participant on an 11-point pain numerical rating scale (PI-NRS, where 0 = no pain and 10 = worst possible pain), foot function using the 5 point Foot Function Index (FFI-5pt) and foot disability using the FPDI [17,24,25]. The FFI-5pts has been translated into Dutch and validated for similar participants as an interview schedule. The FPDI has been validated for participants with foot problems but was not yet available in Dutch. Within the scope of this trial the FPDI has been translated into Dutch and will be validated according to methods proposed by Beaton et al.[26]. Secondary outcomes include social participation (Keele Assessment of Participation[27]) and Quality of Life (SF-12). Both primary and secondary outcome measures will be collected at baseline and after 3, 6, 9, and 12 months. Data on personal education and work history, shoe history and co-morbidity[28] are collected at baseline as possible effect modifiers or confounders.

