### Sample size

There are no evidence-based estimates for clinically important change in assessing forefoot pain or for clinically relevant differences between interventions for chronic foot pain. In a previous study it was estimated that a reduction of approximately two points on an 11-point pain intensity numerical rating scale represents a clinically important improvement [29]. We assume that the improvement in the podiatric treatment group will be one point larger than the improvement in the control group (a mean improvement of approximately 2 versus 1 point on the 0-11 point NRS, with an estimated standard deviation of 2.5). In this design the main question is "whether the podiatric treatment is more effective than the control treatment viz. a standardised shoe advice". Therefore we will perform a one-sided statistical test with the null hypothesis that podiatric treatment has either an equal outcome or a worse outcome as compared to standardised shoe advice, both outcomes having an equal clinical consequence [30].

In order to detect a 1 point difference in improvement between the groups after 12 months with a one-sided significance level of 0.05, and assuming a power of 0.8, an ICC between podiatrists and GPs of 0.05, a correlation of 0.50 between repeated measurements and a minimum of 5 patients per care provider, we would need complete data of 75 participants in each study group. We will enrol 2 × 100 patients to allow for a drop-out rate during follow-up of 25%. If every podiatrist will treat a minimum of 5 patients, 15 podiatrists will be needed to deliver the treatment in the entire intervention group.

In 17 practices of the Academic Network, with a total of n = 23,231 patients of 50 years or older, the diagnosis "foot problems" (ICPC 17) or free text words indicating foot problems were noted in the GP records of n = 497 patients within this age group. This incidence (21/1000) is in accordance with a previous estimate of 17/1000 [31]). We expect that about one third of all consulters presenting with foot problems have forefoot problems that meet our criteria [2,5], and assuming about 50% of these patients are eligible and willing to participate, a practice with a population of average age distribution can generate a minimum of 5 participants per year. This means that we will need to recruit at least 40 practices to participate in the trial to achieve the required number of patients.

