### Treatment allocation and adherence

After providing informed consent, randomisation will be performed based on an allocation schedule that is generated before the start of the trial by a computerised random number generator using block randomisation with blocks of 8 or 4 with pre-stratification for gender and age (<75, ≥ 75). Since the age group ≥ 75 is expected to be smaller, a block of 4 has been chosen to increase the likelihood of equal distribution over the control and intervention groups. An independent research assistant will prepare coded sealed envelopes containing the treatment allocation. After baseline measurements the correct allocation envelope is opened by the participant. The foot examiner will be blinded for the random sequence and will not be informed of the block size ensuring concealed allocation of treatment. All GPs will be notified about the participants' allocated treatment, and will be asked to stimulate adherence to treatment whenever the participant contacts the GP during the intervention period. If symptoms do not improve despite adherence to treatment during the 3 months following randomisation, or with deterioration of the foot problem, the GP is free to provide another treatment or refer the participant for further treatment elsewhere.

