### Data analysis

Multilevel analysis will be used to estimate the overall effect of podiatric treatment as compared to standardised shoe advice on the three primary outcome measures (PI-NTR, FFI-5pt and FPDI). Both clustering due to participants being treated by podiatrists and clustering due to repeated measurements within the same individuals will be taken into account. Results will be adjusted for differences in baseline similarity, if these occur. The effect of interest is the treatment × time interaction [32] where the primary focus will be on the primary outcome measures at 3 and 12 months' follow-up. Differences in secondary outcome will be estimated using similar statistical methods. All data will be analysed using an intention-to-treat approach. In all cases, a significance level of 5% is pre-stipulated.

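### Pain NRS and FPDI appear to be scored twice before allocation, but the described analysis uses no screening score and adjusts for baseline only if imbalance is seen; using both would cut residual variance of pain NRS by about 2–11%

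*Protocol article*

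**What the plan says.** Under Inclusion procedure, the screening questionnaire goes to all potentially eligible patients. On it, "Forefoot pain intensity is scored using a 0-10 point numerical rating scale and the location of pain is indicated on a foot manikin", and foot disability is measured with the FPDI. Under Primary and secondary outcome measures, pain NRS and FPDI are two of the three primary outcomes, and "Both primary and secondary outcome measures will be collected at baseline and after 3, 6, 9, and 12 months".

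The Abstract (Methods) names screening and baseline as two steps: "Inclusion and exclusion criteria will be assessed by a screening questionnaire and baseline assessment". Treatment allocation and adherence places both before allocation: "After baseline measurements the correct allocation envelope is opened by the participant".

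Data analysis does not mention the screening scores. Its only rule on adjustment is "Results will be adjusted for differences in baseline similarity, if these occur". It also states that "The effect of interest is the treatment × time interaction", with the focus on 3 and 12 months. The only correlation in the article is under Sample size: "a correlation of 0.50 between repeated measurements".

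**The concern.** A score taken before allocation can be a covariate without risk of allocation bias. Its value lies in how well it predicts follow-up, not in whether the groups happen to differ on it. The stated rule makes adjustment depend on observed imbalance, so precision available from pre-randomisation scores is used only by chance. A screening score would have no place under that rule.

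With a correlation of 0.50, one baseline score explains only a quarter of the follow-up variance. A second, separately measured score averages out part of the noise in the first and explains somewhat more. At stake is a modestly narrower confidence interval from data the trial already holds. The validity of the comparison is not at stake.

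**Working it through.** **Inputs from Sample size:** difference 1 point; SD 2.5 (variance 6.25); one-sided alpha 0.05; power 0.80; ICC 0.05; at least 5 patients per provider; correlation 0.50; 75 completers per group.

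**Assumption:** the screening–baseline correlation *r* is not given, so it is varied from 0.5 to 0.9.

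**1. The plan's own figure.**
- Unadjusted: n = 2 × (1.645 + 0.842)² × 6.25 / 1² ≈ 77.3 per group.
- Baseline adjustment multiplies by 1 − 0.50² = 0.75. The design effect is 1 + (5 − 1) × 0.05 = 1.2.
- 77.3 × 0.75 × 1.2 ≈ 69.6, so 70 per group (71 with the t-distribution).
- The plan states 75. Using 6 patients per podiatrist, a figure the Discussion mentions, gives a design effect of 1.25 and 73–74; 75 is also 15 podiatrists × 5. The stated number is on the safe side, is not criticised here, and is used below.

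**2. Residual variance at one follow-up time.** With each pre-randomisation score correlating 0.50 with follow-up:
- one score: 1 − 0.50² = 0.750;
- two scores: 1 − 2 × 0.50² / (1 + *r*).

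**3. Power at 75 per group.** SE = √(2 × 6.25 × v × 1.2 / 75), where v is the residual variance; power = Φ(1/SE − 1.645).

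| Covariates | v | Reduction from 0.750 | Power |
|---|---|---|---|
| Baseline only | 0.750 | – | 82.6% |
| Both, r = 0.5 | 0.667 | 11.1% | 86.3% |
| Both, r = 0.7 | 0.706 | 5.9% | 84.5% |
| Both, r = 0.8 | 0.722 | 3.7% | 83.8% |
| Both, r = 0.9 | 0.737 | 1.8% | 83.1% |

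For baseline only, SE = √0.15 = 0.387. For *r* = 0.5, SE = √0.1333 = 0.365. In sample-size terms, 75 completers analysed with both scores are worth 75 × 0.750/0.667 ≈ 84 with baseline alone at *r* = 0.5, and 75 × 0.750/0.706 ≈ 80 at *r* = 0.7.

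**4. Sensitivity.**
- *Screening score less predictive.* With correlations 0.50 (baseline) and 0.40 (screening) with follow-up, R² = (0.25 + 0.16 − 2 × 0.50 × 0.40 × *r*) / (1 − *r*²). At *r* = 0.5, R² = 0.280 and the reduction is 4.0%. At *r* = 0.7, R² = 0.255 and it is 0.7%.
- *Clustering variance untouched by the covariate.* Adding 0.05 × 4 = 0.20 to both variances gives 0.083/0.950 = 8.8% at *r* = 0.5 and 0.044/0.950 = 4.6% at *r* = 0.7.
- *Change score instead of covariate adjustment.* Replacing baseline by the mean of two scores changes the variance from 1 to 1 + (1 + *r*)/2 − 2 × 0.50, which is 0.75 at *r* = 0.5 and 0.85 at *r* = 0.7: a reduction of 25% or 15%.

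**5. FPDI.** The article gives no SD and no FPDI-specific correlation, so no figure can be derived.

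**The case against.** The strongest objection is that a second score may not exist. Foot examination itemises the pre-allocation visit and lists neither NRS nor FPDI, and the only pre-allocation questionnaire described in detail is the screening one. If its scores serve as the baseline values, the gain is zero. This stands as a condition. Separate scores are the more natural reading, because screening and baseline are named as distinct steps and the outcomes have their own baseline collection, but they are inferred.

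Second, this is a condensed article, and the choice of covariates may be settled in an analysis plan that is not shown. A reader might infer that the trial will never use the screening scores; the document supports only that the analysis described here does not. The point survives because the article does fix a rule, conditional adjustment, and that rule points away from using them.

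Third, the size is uncertain. Only the 11% end uses the plan's own correlation. Two scores both taken before treatment may well correlate more strongly with each other than either does with 12 months, which shrinks the gain. The calculation also simplifies the plan: it takes a single time point with baseline always included, whereas the plan describes a repeated-measures model with conditional adjustment. Other estimators can gain more, as the change-score case shows.

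Fourth, the FPDI informs eligibility. Selection on the screening FPDI may narrow its range and weaken its prediction of follow-up. That acts before allocation and so does not bias the comparison, but it may make the gain smaller.

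Finally, a reader might infer that the trial is sized too tightly without the second score. It is not: with baseline adjustment, power at 75 per group is 82.6%, above the planned 80%.

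**Conclusion.** The point holds as an optional gain in precision, not as an error or contradiction. For a baseline-adjusted pain NRS comparison at one follow-up time, adding a separate screening score lowers residual variance by up to about 11% if every pair of measurements correlates 0.50, and by about 2–6% if screening and baseline correlate 0.9–0.7. Power moves from 82.6% to at most about 86%.

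This rests on three conditions: the two scores are separate measurements, the screening score predicts follow-up as well as the baseline score does, and the baseline score is in the model in any case. The last is not what the article currently says. For FPDI only the direction can be stated.

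**What to change.** State under Primary and secondary outcome measures whether the baseline pain NRS and FPDI are measured separately from the screening questionnaire.

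In Data analysis, replace the conditional rule for these two outcomes. The models always include the baseline score as a fixed covariate, whatever imbalance is observed. Where the screening score is a separate measurement, it enters as a second fixed covariate, or the mean of the two scores is used. Choose one form in advance.

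The cost is two or three sentences and at most one extra parameter per model. No extra patients or data collection are needed.

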### Foot examination

A foot examination will be performed at baseline before randomisation to assess eligibility. Additionally, 25 participants from the podiatry group will be asked to attend a second foot examination after three months to enable the process evaluation (see process evaluation of podiatric treatment). The presence of diabetic neuropathy in the forefoot will be ruled out based on tests using a 10 gram Weinstein monofilament and a 64 Hz tuning-fork. With the participant having his or her eyes closed, the skin on the plantar skin of the hallux and the MTP joints of I and V will be touched with the monofilament, and two out of three touches must be perceived. The vibrating tuning-fork is placed on the medial side of MTP1 and on the lateral side of MTP5; the vibration must be perceived for more than 5 seconds. Digital photographs of the ventral, lateral and medial side of the foot and shoes will be taken on a surface containing measurement lines in centimetres. Participants will be asked to bring the shoes they wear most often for this assessment and for the pressure measurements. Next, the Foot Posture Index will be assessed and scored according to Redmond et al.[19]. To assess pressure distribution patterns during barefoot and shod gait Emed-X (Novel gmbh, Münich, Germany) [20] and Pedar-X (Novel gmbh, Münich, Germany) [21,22] will be used. The Emed platform (4 sensors per cm2, sample frequency 100 Hz) is imbedded in a polyethylene walkway. A two-step protocol will be used for the barefoot pressure measurements, and each foot will be measured 3 times [23]. Each participant will be asked to walk at their preferred speed and with their preferred step length, in other words "as normally as possible". Everyone will have at least two practice runs per foot before the actual measurements are made. Participants are asked to look straight ahead to prevent targeting; if targeting is suspected, the measurement will be discarded and a new run will be executed. For the in-shoe pressure measurements an adequate size sensor-insole will be placed in the shoe (99 sensors/insole, 100 Hz). Participants will be asked to walk back and forth until twelve steps per foot are obtained. First steps, final steps and steps while turning will be excluded from the measurements.

